### Outcome measures

The primary outcome is the change from baseline in the Alzheimer’s Disease Assessment Scale-cognition (ADAS-cog) [21] score measured at week 12. The maximum score of the ADAS-cog is 70 including 15 items of cognitive dysfunction assessment. The higher values indicate higher degree of deficit [22].

The secondary outcomes include the following items: the change from baseline in the ADAS-cog score measured at week 36. The change from baseline in total MMSE score [23], in the Alzheimer’s Disease Cooperative Study-Activity of Daily Living (ADCS-ADL) score, and in the Quality of Life-Alzheimer’s Disease (QOL-AD) score measured at weeks 12 and 36. The MMSE score is commonly used for estimating the severity of cognitive impairment with a maximum score of 30. The questions in this scale included orientation to time, orientation to place, attention and calculation, recall of three words, and visual construction. The ADCS-ADL score contains 19 domains about assessment of basic and operational ability of daily living [24]. The QOL-AD score, which includes physical health, mental health, social and financial assessment, and quality of life domains, is completed by both patients and caregivers [25].

All the adverse events will be recorded and assessed throughout the whole study period. Adverse reactions related to acupuncture may be fainting, hematoma formation, local infection or skin pain. Individuals who develop severe complications will be excluded from continuing in study, and the reasons for their termination will be recorded.

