### Sample size and statistical analysis

The calculation of sample size is based on the primary outcome which is the change from baseline in the ADAS-cog score. According to previous studies [26], 39% of patients showed an improvement of at least 4 points on the ADAS-cog score after being treated with donepezil. We estimated the rate to be 39% in the donepezil group and 55% in the EA combined with donepezil group. Three hundred and four participants were needed to provide 80% power at a significant level of 5% using analysis of variance. The total sample size required for the study is 334 (167 each group) assuming a 10% loss to follow-up.

Baseline score of the ADAS-cog and age will be used as a covariate when assessing the differences between the EA combined with donepezil group and the donepezil group by an analysis of covariance for the primary and the secondary variables if data fits the normal distribution. Otherwise, a nonparametric test will be used to compare the statistical difference between the two groups. All the data will be blindly analyzed by the statisticians from the Clinical Evaluation Center of Guang’anmen Hospital. SPSS 20.0 (IBM Corp., Armonk, NY, USA) statistical software will be used for the statistical analyses. Subanalysis will be applied to the statistical analysis according to the severity of the condition of participants measured by the ADAS-cog [27]).

Efficiency and safety analysis will be based on all the participants at randomization according to the intention-to-treat (ITT) principle. Missing values assumed missing at random will be handled by the multiple imputation method [28]. Continuous data will be presented by the average and standard error. Two-sided tests will be used for all outcomes. A *P* value of less than 0.05 is considered to show statistical significance.

For the safety assessments, a description on the adverse events and adverse reactions will be presented in tables. These tables will include the categories, severity, rate of incidence, and correlation with the treatment. Individuals with serious adverse events should stop receiving the intervention and details will be reported in a timely manner.

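### Change in MMSE, ADCS-ADL and QOL-AD is adjusted for baseline ADAS-cog rather than for the scale's own baseline, which costs precision in six of the seven secondary analyses

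*Protocol article*

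**What the plan says.** In the protocol article, under Sample size and statistical analysis, the covariate rule reads "Baseline score of the ADAS-cog and age will be used as a covariate when assessing the differences between" the two arms. The sentence goes on to say that this is done "by an analysis of covariance for the primary and the secondary variables if data fits the normal distribution". If the normality condition fails, "Otherwise, a nonparametric test will be used to compare the statistical difference between the two groups"; no covariate is named for that branch.

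Under Outcome measures, the primary outcome is change in ADAS-cog at week 12. The secondary outcomes are:

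- "the change from baseline in the ADAS-cog score measured at week 36" (one analysis);
- "The change from baseline in total MMSE score", and likewise change in ADCS-ADL and in QOL-AD, each at weeks 12 and 36 (3 × 2 = 6 analyses).

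That makes seven secondary analyses. No sentence in the article adds the baseline of MMSE, ADCS-ADL or QOL-AD to the model.

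**The concern.** A change score contains its own baseline with a negative sign. With equal spread at both visits it is therefore correlated with that baseline whenever the baseline-to-follow-up correlation is below 1. Removing that dependence is the usual reason to analyse change by analysis of covariance, and it needs the outcome's own baseline in the model. The baseline of a different scale removes only the part that the two scales share.

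For ADAS-cog the stated rule is right. Carried over to the other three scales, it leaves residual variance that data already in hand could remove, and it lets a chance difference in a scale's own baseline move the estimate in the trial at hand. At stake is the precision of the evidence on function, quality of life and a second cognitive scale.

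**Working it through.** **Frame.** The article's sample size reproduces. It states "We estimated the rate to be 39% in the donepezil group and 55% in the EA combined with donepezil group". With a two-sided 5% level, 80% power and pooled variance (mean rate 0.47):

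n per arm = [1.960·√(2 × 0.47 × 0.53) + 0.842·√(0.39 × 0.61 + 0.55 × 0.45)]² / 0.16² = (1.383 + 0.586)² / 0.0256 ≈ 151.6, so 152 per arm and 304 in total. Then 304 × 1.10 = 334.4, the stated 334 (167 per arm).

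This rests on ADAS-cog response rates only, so the choice of covariates for the other scales does not touch it.

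**Inputs for the check.** The article gives no correlations and no SDs for these scales, so the following are assumptions:

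- SD 1 at baseline and at follow-up;
- p, the baseline-to-follow-up correlation within a scale, 0.5 to 0.8;
- r, the correlation of baseline ADAS-cog with the other scale's baseline, 0.2 to 0.7;
- baseline ADAS-cog related to follow-up only through the scale's own baseline;
- age left out of the comparison.

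**Residual variance of the change score**

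- Adjusted for baseline ADAS-cog: 2(1 − p) − r²(1 − p)²
- Adjusted for own baseline: 1 − p²
- Difference: (1 − p)²(1 − r²), never negative

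**Chance imbalance.** The difference in baseline means between arms has standard error √(2/167) = 0.109 SD. The part that ADAS-cog does not explain is √(1 − r²) of this, and a fraction (1 − p) of that part enters the estimate: 0.109 × (1 − p) × √(1 − r²).

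| p | r | Variance, ADAS-cog adjusted | Variance, own baseline | Variance lower by | SE lower by | Imbalance carried (SD) | 304 patients are worth |
|---|---|---|---|---|---|---|---|
| 0.5 | 0.2 | 0.990 | 0.750 | 24% | 13% | 0.054 | 230 |
| 0.5 | 0.7 | 0.878 | 0.750 | 15% | 8% | 0.039 | 260 |
| 0.7 | 0.5 | 0.578 | 0.510 | 12% | 6% | 0.028 | 268 |
| 0.8 | 0.2 | 0.398 | 0.360 | 10% | 5% | 0.021 | 275 |
| 0.8 | 0.7 | 0.380 | 0.360 | 5% | 3% | 0.016 | 288 |

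The last column is 304 × (own-baseline variance / ADAS-cog-adjusted variance).

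The imbalance column and the variance columns describe one cost in two ways: the square of the carried imbalance is 2/167 times the variance difference. They must not be added together.

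**Sensitivity**

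- Higher within-scale correlation: at p = 0.9 and r = 0.7, 0.195 against 0.190, a standard error only about 1.3% lower.
- Growing spread: if the follow-up SD is s times the baseline SD, the slope of change on own baseline is ps − 1. At p = 0.8 and s = 1.25 it is zero, and own-baseline adjustment gains nothing.

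**Validity.** A simulation with no treatment effect, 152 per arm and 4,000 runs at each of six settings (p = 0.5, 0.7, 0.9; r = 0.3, 0.7) gave mean ADAS-cog-adjusted estimates within 0.002 SD of zero and type I error of 4.5% to 5.15%. At p = 0.7 and r = 0.3 the simulated standard errors were 0.0871 (ADAS-cog adjusted) and 0.0808 (own baseline), in line with the formula.

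**The case against.** The strongest reply is that the article is a condensed text written around its primary outcome. It says which covariates will be used, does not say that no others will be, and the model terms for each outcome may sit in an unseen analysis plan. This carries some weight, but the article does not leave the matter open: it names one scale and extends it expressly to the secondary variables. A plan that followed it literally would omit the own baselines.

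A second reply is that ADAS-cog is the trial's severity measure, so adjusting for it has a rationale. That is true. It is a reason to allow baseline ADAS-cog as an extra covariate, not a reason to leave out the own baseline.

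Third, the gain depends on correlations and SDs that the article does not give, and it can shrink to almost nothing. This stands and limits the weight of the point.

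Fourth, the rule holds only if the data are judged normal. This also stands. The fallback names no covariate, so it does not supply the missing adjustment either.

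A reader might infer more than the article supports:

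- That every secondary outcome has the wrong covariate. Not so: ADAS-cog at week 36 is adjusted for its own baseline.
- That the comparisons are biased or invalid. Allocation is randomised 1:1, so they are unbiased on average and the error rate holds.
- That baseline ADAS-cog explains next to nothing of QOL-AD. The article has no figure on this.

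**Conclusion.** The point holds for MMSE, ADCS-ADL and QOL-AD at both time points: six of seven secondary analyses, or eight of nine if patient-rated and caregiver-rated QOL-AD are analysed separately. As written, the rule adjusts these changes for another scale's baseline and not their own.

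The cost is precision, together with bias conditional on a chance imbalance in the scale's own baseline. Under the assumed ranges and equal SDs, own-baseline adjustment would lower residual variance by about 5 to 24% and the standard error by about 3 to 13%. A typical chance imbalance carries about 0.016 to 0.054 SD into the estimate. These figures are illustrations over a range, not estimates for this trial. Since the primary analysis and the sample size are unaffected, the severity is modest.

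**What to change.** Reword the covariate rule along these lines: where analysis of covariance is used, each continuous outcome is analysed with its own baseline value and age as covariates; baseline ADAS-cog may be kept as an additional covariate. If patient-rated and caregiver-rated QOL-AD are analysed separately, each takes its own baseline. The ADAS-cog analyses at weeks 12 and 36 stay as they are.

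The cost is one sentence. The baselines must be collected anyway to compute change, so no data, visits or patients are added. Making the change before the data are analysed also avoids a later choice of covariates that could look driven by the results.

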## Methods/Design

This trial is a prospective, randomized controlled, clinical trial to be conducted between June 2017 and December 2019. Three hundred and thirty-four participants with AD will be recruited at Guang’anmen Hospital, Beijing, China via the hospital web or posters. Recruiting and screening will be in the charge of a research assistant, whereas the diagnosis will be made by a neurologist. A 2-week baseline assessment will be conducted. Randomization is performed by the pharmacological assessment center at Guang’anmen Hospital. The participants identified as eligible will be randomized into two groups—EA combined with donepezil and donepezil—at a ratio of 1:1. The random block is set to 4, and random grouping is produced by using the Statistics Analysis System (SAS) software. Random numbers and information about grouping are sealed into opaque envelopes with correlative sequence numbers of entering the trial marked on the outside. Acupuncturists will open the envelopes according to the sequence numbers. The flowchart of the trial is shown in Fig. 1. The total study period of this trial is 38 weeks (Fig. 1), including 2-week baseline assessment, 12-week treatment period and 24-week follow-up period.

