### Intervention

#### EA combined with donepezil group

The acupoints are GV 16, GV 20, GV 24, and *Shang Yintang* (up to GV 29 1 cun), as well as bilateral EX-HN 5 and KI 4. The location of the acupoints is based on the *The Name and Location of Acupoints* drafted in 2006 by the National Standard of the People’s Republic of China (GB/T 12346-2006). The acupuncture protocol is based on reviews of acupuncture for AD [18, 19] published and expert consensus. Acupuncturists who have at least 2 years of practical experience will perform the intervention. Disposable, sterilized needles made of stainless steel (Hwato, Suzhou Medical Appliance Factory, Suzhou, China) and electric stimulators (SDZ-V electroacupuncture apparatus, Suzhou Medical Appliance Factory, Suzhou, China) will be used in the treatment group. After routine disinfection, the GV 16 will be needled while participants are in the sitting position with their head slightly forward and their muscles relaxed. The needle (25 mm in length) will be inserted obliquely and slowly downward toward the mandibular direction to a depth of 12.5 mm. The needle will be immediately removed after “*de qi*” (*de qi*, which is very important to therapeutic effect, is a sensation of soreness, heaviness, and numbness when needling [20]) and not retained. *Shang Yintang*, GV 20, and GV 24 will be needled (40 mm in length) at a 30° angle to a depth of approximately 12.5 mm while participants are in the decubitus position. For bilateral EX-HN 5 and KI 4, the needle (40 mm in length) will be vertically inserted to a depth of 25 mm. The electric stimulator will be applied to GV 20, GV 24, and bilateral EX-HN 5 with a spare-dense wave of 10/50 Hz, 0.5–5.0 mA. The current intensity is set up to the maximum tolerance of patients. There are three sessions per week with each session lasting for 30 min. There will be 12 weeks of treatment with 36 sessions for each participant in total. EA treatment will last for 12 weeks.

Donepezil (Eisai Pharmaceuticals, Shanghai, China) 5 mg will be given once daily before bed-time for the first 4–6 weeks. Based on the treatment effect, the dosage may be increased to 10 mg once daily before bed-time for the next 6–8 weeks. Donepezil will be taken for continuously for 24 weeks.

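### The intention-to-treat set is fixed as the safety population, so never-needled participants count in the denominator for electroacupuncture reactions

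*Protocol article*

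**What the plan says.** The Sample size and statistical analysis section of the protocol article gives one population rule for both efficacy and harms: "Efficiency and safety analysis will be based on all the participants at randomization according to the intention-to-treat (ITT) principle". It names no separate safety set. The next sentence gives the missing-data rule: "Missing values assumed missing at random will be handled by the multiple imputation method".

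The same section describes the safety output as descriptive tables of adverse events and adverse reactions: "These tables will include the categories, severity, rate of incidence, and correlation with the treatment".

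Under Outcome measures, the collection rule is: "All the adverse events will be recorded and assessed throughout the whole study period". The expected needling harms are also listed there: "Adverse reactions related to acupuncture may be fainting, hematoma formation, local infection or skin pain".

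On exposure, the section on the EA combined with donepezil group says: "There will be 12 weeks of treatment with 36 sessions for each participant in total". Methods/Design sets the total study period at 38 weeks, "including 2-week baseline assessment, 12-week treatment period and 24-week follow-up period".

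**The concern.** Analysis by allocated arm is the cautious choice when the question is whether a treatment works, because non-adherence pulls the arms together and makes a benefit harder to show. For harms the same pull works the other way: it makes the added treatment look safer.

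The reactions listed for acupuncture arise from needling. An EA-arm participant who withdraws before the first session cannot have one, yet adds to the denominator. A control who obtained EA could have one, and it would be reported in the donepezil-only arm.

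This is a stated rule, not a gap that an unseen analysis plan could fill. A plan that follows the sentence inherits the problem, and one that departs from it contradicts the protocol. At stake is whether the safety tables describe people who were actually exposed to EA.

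**Working it through.** **The plan's own figures.** The article gives no adverse event rate, so there is no safety figure to reproduce. The only planned number used below is the arm size, 334 / 2 = 167. The sample size behind it does reproduce: 39% versus 55%, two-sided 5%, 80% power and pooled variance give 152 per arm, or 304, and 304 × 1.1 = 334.4, stated as 334. Nothing below changes it.

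**Step 1: EA-arm reaction risk.** Let r be the reaction risk in people who are needled and u the share of the EA arm never needled. The risk reported on all randomised participants is r × (1 − u). Both inputs are assumptions. The top of the range for u borrows the plan's 10% loss to follow-up, which would require every loss to occur before the first session.

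| u | r = 5% | r = 10% | r = 20% | Expected cases among 167 at r = 10% |
|---|---|---|---|---|
| 1% | 4.95% | 9.9% | 19.8% | 16.5 |
| 2% | 4.9% | 9.8% | 19.6% | 16.4 |
| 5% | 4.75% | 9.5% | 19.0% | 15.9 |
| 10% | 4.5% | 9.0% | 18.0% | 15.0 |

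At u = 10%, 167 × 0.90 = 150.3 people are needled and 15.0 react. Dividing by 167 gives 9.0%; dividing by 150.3 gives the true 10%. The relative understatement always equals u.

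**Step 2: any control who obtained EA.** If a share c of controls were needled, the between-arm difference in reaction risk would be r × (1 − u − c). At r = 10%, each 1% of controls needled removes a further 0.1 percentage points. The article gives no value for c.

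**Step 3: the all-cause contrast over weeks 1–12.** With background risk b and EA excess e, the risk difference under allocation is (1 − b) × e × (1 − u). With b = 10% and e = 10% (both assumed), it is 9.0 points at u = 0, 8.8 at 2%, 8.6 at 5% and 8.1 at 10%.

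**Step 4: what a pooled window would do.** This bears only on the optional part of the fix, because the article does not say that weeks are pooled. EA covers 12 of the 36 weeks from the start of treatment. Assume constant background risk and a 10% EA excess confined to weeks 1–12, so that background risk over 36 weeks is 1 − (1 − b)³.

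| Background risk in 12 weeks | Risk ratio, weeks 1–12 | Risk ratio, 36 weeks | Risk difference in points, 12 → 36 weeks |
|---|---|---|---|
| 5% | 2.90 | 1.60 | 9.5 → 8.6 |
| 10% | 1.90 | 1.27 | 9.0 → 7.3 |
| 20% | 1.40 | 1.10 | 8.0 → 5.1 |

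These are all-cause contrasts. The number and proportion of participants with a needling reaction do not change with a longer window. The excess event count does not change either: if EA doubles an assumed 0.1 events per person per 12 weeks, the excess is 33.4 − 16.7 = 16.7 events over 12 weeks and 66.8 − 50.1 = 16.7 over 36 weeks.

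**The case against.** The strongest reply is that the effect is small and that the plan already has a safeguard. The 10% figure is an allowance for loss to follow-up, not a forecast of people never needled, so the real share is probably nearer the lower end of the range. Controls are meant to receive donepezil only, so crossover is hypothetical. The tables are to show relation to treatment, and acupuncture reactions are listed by name, so needling harms can be read apart from background events. Grouping by treatment received also gives up some of the protection of randomisation.

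Most of this stands, and it limits the size of the point. It does not remove it. Labelling an event as related to treatment leaves the denominator as it was. The Discussion also concedes that participants cannot be blinded, so attribution should not be the only safeguard.

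A reader might infer three stronger claims, which the article does not support:

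- **That safety is analysed over all 38 weeks pooled.** Outcome measures sets a window for recording and assessing events, which is sound practice. No summary window is fixed, and that detail can properly sit in an analysis plan.
- **That baseline events are counted as treatment events.** The safety sentence starts from randomised participants, and Methods/Design describes the baseline assessment before randomisation. Nothing says that such events enter the treatment tables.
- **That adverse events are imputed.** The imputation sentence speaks of missing values in general. Nothing says that an unreported event is treated as a missing value.

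**Conclusion.** The point holds in a limited form. Placing safety on all randomised participants by allocated arm is an explicit choice, and it biases the harms comparison towards no added risk. On the EA arm's reaction risk the bias is 1% to 10% in relative terms if 1% to 10% of that arm are never needled, and the upper end is an extreme case. Any needled control would add to it in the same direction. These shares and the reaction risks are assumptions. The direction follows from the rule itself, provided that someone in the EA arm goes un-needled or someone in the control arm is needled.

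This would not by itself overturn a safety conclusion, but it is worth correcting because the present wording commits the trial to the less suitable population.

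**What to change.** In Sample size and statistical analysis:

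1. Limit the intention-to-treat sentence to efficacy.
2. Limit the multiple-imputation sentence to efficacy outcomes. This is a clarification only.
3. Add that safety is analysed on participants who received at least one EA session or one donepezil dose, grouped by treatment actually received, using observed events.
4. Optionally, show a weeks 1–12 summary beside the full-period one, so that all-cause contrasts are not weakened should EA and non-EA weeks be combined.

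The cost is a few words, one extra table if item 4 is adopted, and possibly a slightly less favourable EA reaction rate. The sample size is unaffected. The article does not say that session attendance and event dates are recorded. The first is needed for item 3 and the second for item 4, so the trial team should confirm that the case report form captures them.

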### Quality control

All of the investigators participating in this trial will take a training course which lasts for 1 day. The assessment of all the scales will be in the charge of the research assistants who do not know the distribution of groups. Members of an independent Data Monitoring Committee (DMC) will regularly inspect the data and monitor the trial progression before the data statistics. Data management and statistical analysis will be under the control of the statisticians.

### Ethics and dissemination

This study has been approved by the Ethics Committee of Guang’anmen Hospital, CACMS (2015EC043). This protocol was written following the Standard Protocol Items: Recommendations for Interventional Trials (SPIRIT) Checklist (Additional file 1) and figure (Fig. 2). All important protocol modifications will be submitted to the Ethics Committee of Guang’anmen Hospital. All participants and caregivers will be informed about the potential risks and benefits of the study. Informed consent will be obtained for either all participants or, if their capacity to consent is absent, their nearest relatives or their caregivers. All personal information about participants will be prohibited from other use and stored in specific cabinets in order to protect confidentiality before, during, and after the trial. Statistical and monitoring managers will have access to the final trial dataset. For compensation to those who suffer harm from trial participation, we will provide free corresponding therapies and medical consultation. The results of this trial are planned to be disseminated in conferences or publications.

